### Trial design {8}

This is a multi-site phase II, parallel, non-inferiority randomized clinical trial that aims to compare the short- and medium-term effects of ICAU at three military sleep clinics versus CBTI delivered remotely through digital CBTI hubs. ICAU and the digital CBTI hubs will be evaluated and compared on an insomnia outcome measure as well as patient-rated treatment satisfaction and daytime mood and anxiety symptoms. In alignment with the pragmatic nature of this study and, if successful, the aim to rapidly inform insomnia care practices, this trial is designed to minimize disruption of each sites’ current processes for the diagnosis of insomnia and subsequent insomnia treatment procedures. All sites will follow their standard procedures for service members with complaints of sleep disturbances to obtain an appointment with the site’s sleep medicine clinic for an initial evaluation. Following this appointment, service members who receive a diagnosis of chronic insomnia by their sleep medicine provider and who would otherwise be referred (internally or externally) for CBTI will be referred to the study. After providing informed consent, eligible participants will complete baseline assessments including validated self-report questionnaires on insomnia, anxiety, depression, and sleepiness. Participants will then be randomized to either ICAU or insomnia care delivered via a digital CBTI hub. ICAU will be delivered synchronously, in-person (face-to-face or virtual) according to each site’s current standard of care and in the real-world clinical practice setting by a non-research clinician. While there are practice overlaps across sites, some variation exists in procedural and clinical treatment approaches and delivery formats (e.g., required attendance at a sleep seminar in addition to individual sessions, emphasis given to the cognitive component of CBTI, in-person versus synchronous telehealth, and scheduled session frequency). To maximize the generalizability of findings to current clinical practices, ICAU will not be standardized across sites or clinicians. All ICAU clinicians will deliver insomnia care to study participants as they would otherwise treat patients with chronic insomnia who are not participants in this clinical trial. Insomnia care delivered via the digital CBTI hubs includes the first-line recommended treatment for insomnia, CBTI, delivered remotely and asynchronously with NOCTEM’s clinical decision support platform called COAST by a NOCTEM-certified and licensed clinician. A follow-up will be conducted with participants randomized to both treatment arms 6–8 weeks after baseline and again 3 months later.

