#### Intervention description {11a}

Both intervention delivery formats, ICAU, and digital CBTI hubs using COAST will be delivered by credentialed masters or doctoral-level clinicians with experience in behavioral sleep medicine and include CBTI techniques. CBTI is a multi-component manualized cognitive-behavioral treatment protocol for the treatment of insomnia that is widely available. Among the various techniques that can be combined into CBTI, the most effective techniques to reduce insomnia are stimulus control and sleep restriction [40, 41]. Stimulus control aims to limit the use of the sleep environment (bed, bedroom) to sleep and directly addresses behaviors that disrupt circadian sleep–wake regulation mechanisms [42–44]. Sleep restriction involves the implementation of a regular sleep–wake schedule, which limits the time spent in bed while awake [45]. Relaxation techniques (e.g., progressive muscle relaxation, deep breathing, guided imagery) may also be helpful to reduce cognitive or physical hyperarousal that delays sleep onset [17].

Specifically, ICAU will include the usual care for service members diagnosed with insomnia at their local military treatment facility, as per the site’s current clinical practices. Treatment sessions will be conducted with the treating clinician(s) who typically receive insomnia referrals. Across sites, treatment duration will range from approximately 6 to 12 weeks with appointments scheduled every 1 to 3 weeks. Sleep metrics and progress will be evaluated and assessed by sleep diary, validated measures such as the Insomnia Severity Index and Epworth Sleepiness Scale, and patient self-report during scheduled sessions. All sessions will be conducted synchronously and in person (face-to-face, virtually). Patients may be required to attend a single sleep hygiene group seminar where foundational healthy sleep habits and relaxation skills are reviewed.

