Treatment via a digital CBTI hub includes CBTI delivered remotely and asynchronously via NOCTEM’s proprietary software platform COAST (Clinician Operated Assistive Sleep Technology) with a NOCTEM research clinician. All research clinicians are fully credentialed, licensed healthcare professionals certified in the use of COAST by NOCTEM. COAST is an adaptive digital health system that includes a clinician portal for prospective monitoring of side effects, progress, and adherence and algorithm-generated recommendations for the implementation of CBTI techniques; a patient application (“app”) with embedded sleep educational materials and self-report daily sleep diary and weekly assessments; and a secure HIPAA-compliant two-way messaging system that allows patients and clinicians to communicate directly in case of questions. Treatment sessions will be conducted across 6–8 weeks, with asynchronous clinical interactions occurring throughout the 6–8-week period with at least one interaction per week. Minimally, each week, the research clinician will send personalized recommendations for behavioral changes to the participant via the app and instruct the participant to review specific sleep tactics (written or audio CBTI interventional materials) that provide instruction on how to implement and the background for the CBTI techniques. Dialog regarding these recommendations will primarily be conducted via the COAST messaging system; however, at any time during the intervention, the participant or the clinician may request a synchronous telephone or in-person appointment.

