#### Participant timeline {13}

The total duration of participation is up to 5 months. Figure 1 displays the schedule of enrollment, interventions, and assessments for the primary outcomes of interest.

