Our primary strategy will compare digital CBTI hubs and ICAU using analyses that are straightforward and highly interpretable while still accounting for other important covariates. We will use analysis of covariance (ANCOVA) to determine whether ISI at 6–8 weeks and at 3-month follow-up differs between digital CBTI hubs and ICAU after controlling for baseline ISI and other relevant covariates. Cohen’s *d* effect sizes (*d* ESs) with 95% CIs estimated from the ANCOVA model will be calculated and compared to the NIM as outlined above. To examine more nuanced effects across time, we will calculate the rate of change in ISI symptoms (ΔISI) across baseline, 6–8 weeks, and 3-month follow-up for each individual and then use linear regression to compare ΔISI between digital CBTI hubs and ICAU after controlling for relevant covariates. We will also model the repeatedly measured outcome using mixed effects models with a random intercept and slope. Cohen’s *d* ESs and 95% CIs estimated from these models will be calculated and compared to the NIM as outlined above.

For non-inferiority tests, we set an allowable one-sided type I error rate of *α* = 0.025. Conservatively adjusting for our two a priori *t*-tests (6–8 weeks and 3-month follow-up), we use *α** = 0.0125 to determine power. Our full sample size of 94 per group will provide 0.88 power. However, even with attrition of 25% (*N* = 70 completers per group), we expect to have 0.80 power. We will use the same statistical approach to assess and compare changes in depression and anxiety symptom severity at 6–8 weeks and at 3-month follow-up.

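### The supplementary rate-of-change analyses reduce three unequally spaced visits to one slope, can hide a 6–8 week deficit, and are still judged against the 0.50 margin

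*Protocol article*

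**What the plan says.** In the protocol article, the section Statistical methods for primary and secondary outcomes {20a} makes ANCOVA at 6–8 weeks and at 3-month follow-up the primary strategy. It then adds two longitudinal analyses of ISI. The first is introduced with "To examine more nuanced effects across time, we will calculate the rate of change in ISI symptoms". The quantity is "the rate of change in ISI symptoms (ΔISI) across baseline, 6–8 weeks, and 3-month follow-up for each individual", and it is regressed on arm with covariates. The second uses "mixed effects models with a random intercept and slope". Cohen's d and its 95% CI "estimated from these models will be calculated and compared to the NIM as outlined above". The same approach is extended to depression and anxiety.

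On timing, Trial design {8} states: "A follow-up will be conducted with participants randomized to both treatment arms 6–8 weeks after baseline and again 3 months later". Participant timeline {13} adds: "The total duration of participation is up to 5 months". On treatment periods, Intervention description {11a} says of the hub arm "Treatment sessions will be conducted across 6–8 weeks" and of insomnia care as usual (ICAU) that "treatment duration will range from approximately 6 to 12 weeks".

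The article gives no formula for the rate and no coding of time. It does not say how a person with only two visits is handled: section {20c} leaves the missing-data method open until the mechanism has been examined.

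**The concern.** The 6–8 week visit is one of the two test times that the plan fixes in advance, and it falls at the end of hub treatment. The next interval is about twice as long and, for the hub, contains no scheduled treatment. A single rate over all three visits says little about the 6–8 week result. Under the most natural computation it gives that result the wrong sign, so a worse score makes the slope look better.

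This would matter little for a purely descriptive summary. Here, however, the slope-based d is put through the same non-inferiority rule as the visit-specific d. The Sample size {14} section justifies 0.50 from published treatment effect sizes. It offers no basis for 0.50 in units of the between-person SD of slopes. A supplementary result could therefore appear to support non-inferiority where the visit-specific result does not.

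**Working it through.** The plan states no figure for the rate-of-change analysis, so there is none to reproduce.

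**Visit times.** The 6–8 week visit is taken at 7 weeks, and 3 months later adds about 13 weeks. So t = 0, 7, 20 weeks, which fits a participation of up to 5 months.

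**Least-squares weights.** The slope is Σ wᵢyᵢ with wᵢ = (tᵢ − t̄)/Σ(tⱼ − t̄)².
- t̄ = 9; deviations are −9, −2, +11; sum of squares = 81 + 4 + 121 = 206.
- Weights: −9/206 = −0.0437; −2/206 = −0.0097; +11/206 = +0.0534 per week.
- Over the stated window, the middle weight is −0.0124 at 0/6/19 weeks and −0.0074 at 0/8/21 weeks. It is small and negative throughout, because of the spacing alone; no assumed trajectory is needed.
- If the last visit were 13 weeks from baseline, the middle weight would be −0.0039, +0.0039 or +0.0116 for a 6-, 7- or 8-week visit. The quoted timing argues against that reading.

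**Hub deficit at 6–8 weeks only.** Assumed (not in the documents): SDs 4/5/5; correlations 0.40 (baseline and 6–8 weeks), 0.35 (baseline and 3 months), 0.70 (6–8 weeks and 3 months).
- Slope variance × 206² = 81·16 + 4·25 + 121·25 + 2·18·0.40·20 − 2·99·0.35·20 − 2·22·0.70·25 = 2553. Slope SD = √2553/206 = 0.2453 per week.
- Hub 2.5 points worse at 6–8 weeks: visit d = 2.5/5 = +0.50.
- Slope difference = −0.0097 × 2.5 = −0.0243; slope d = −0.0243/0.2453 = **−0.10**.
- With last minus first, the 6–8 week score does not enter, so d = 0.
- Under other assumptions (means 18/10/10, between-person SD 4, within-person SD 3, hub 3 points worse at 6–8 weeks), visit d = +0.60 and slope d = −0.13.

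**Hub deficit at both visits.** With 2.5 points at each and no drop-out, slope d = (−0.0097 + 0.0534) × 2.5/0.2453 = +0.445, taken below as +0.44. A persistent deficit is seen.

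**Drop-out, if two-visit slopes are kept.** Assume a proportion p misses the last visit independently of scores.
- On an assumed path 19/10/10, the three-visit slope is −0.393 per week. The two-visit slope is −9/7 = −1.286, about 3.3 times as steep.
- Two-visit slope SD = √(16 + 25 − 2·0.40·20)/7 = 5/7 = 0.714.
- In each arm, the mean is (1 − p)·m₃ + p·m₂ and the variance is (1 − p)·v₃ + p·v₂ + p(1 − p)(m₃ − m₂)².

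| Scenario | Slope d (hub − ICAU) |
|---|---|
| Identical arms, 19/10/10, drop-out 25% hub v 15% ICAU | (−0.616 + 0.527)/0.525 = −0.17 |
| Same, path 19/13/10 | −0.10 |
| Same, straight path 19/15.85/10 | 0.00 |
| Identical arms, 25% in both | 0.00 |
| Hub 2.5 worse at both visits (19/12.5/12.5 v 19/10/10), 25% in both | (−0.445 + 0.616)/0.535 = +0.32 |

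The 25% is the plan's attrition figure; 15% is assumed. Swapping the two rates reverses the sign of −0.17. Using only people with all three visits gives d of about 0 for identical arms.

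**The case against.** The strongest reply is that much of this is conditional. The article does not define the rate. Last minus first removes the sign reversal, and this is a detail that a condensed article may leave to the SAP. These analyses are also supplementary: the alpha adjustment covers only the two visit-specific tests. In the example above, the primary ANCOVA at 6–8 weeks would itself show about +0.50. When both arms start and end equal, a rate difference near zero is arguably what a baseline-to-end rate should show. All of that stands, and it limits the point to supplementary analyses.

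Three stronger readings are tempting, and the documents support none of them.
- A reader might infer that drop-out will make the hub look better. That needs two-visit slopes, an early plateau and higher hub drop-out together, and the plan states none of these. The plateau fits ICAU less well, since ICAU may continue to 12 weeks. If ICAU improved more slowly or lost more patients, the bias could favour ICAU. An imbalance such as 25% v 5%, which gives about −0.38, has no basis in a plan that expects 70 completers per group.
- A reader might infer that the mixed model forces a straight line. A random intercept and slope describes the random effects; the form of the fixed time effect is not given. The mixed model is not quantified here.
- A reader might infer that the trial's main conclusion is at risk. It is not, because the ANCOVA does not use the slope.

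The objection does not remove the core. Whether computed by least squares or as last minus first, one linear rate reverses or discards the 6–8 week result, and its d is still measured against a margin justified on another scale.

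**Conclusion.** The point holds for the supplementary longitudinal analyses only. With the stated visit times and a least-squares slope, the 6–8 week score carries a weight of about −0.010 per week, which needs no trajectory assumption. Under the assumed SDs and correlations, a deficit at 6–8 weeks equal to the margin (d = +0.50) reads as −0.10, or about 0 if the rate is last minus first. Keeping two-visit slopes adds a conditional effect. At 25% v 15% drop-out, identical arms differ by between 0 on a straight path and −0.17 on a full plateau. Equal 25% drop-out shrinks a true deficit at both visits from about +0.44 to +0.32. The size depends on the formula, trajectory and missing-data rule, none of which is stated, and the direction between arms is open. The primary ANCOVA is unaffected. The plan should be changed here, but the point does not threaten the main analysis.

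**What to change.** For ISI, PHQ-2 and GAD-2, make the supplementary longitudinal analysis a repeated-measures mixed model with visit as a category, arm-by-visit terms, baseline score, site and stratification factors, and an unstructured covariance. Report the hub − ICAU difference at each follow-up visit, with d on the same SD as the primary ANCOVA, so that the 0.50 margin keeps one meaning. If a slope analysis is kept, label it descriptive, define the rate, the time scale and the handling of people with two visits, and do not compare its d with 0.50.

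The change costs wording and different code, with no extra data. The loss is a single rate figure for the non-inferiority comparison.

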#### Sample size {14}

Power calculations and sample size were based on a conservative estimate of the non-inferiority margin (NIM) based on our preliminary data and prior studies [53–55] and effect sizes reported in the literature on the effects of CBTI on insomnia severity [56–60], as well as estimates of recruitment feasibility based on patient volume at the participating sites. Specifically, effect sizes in the moderate to very large range (0.50 to 2.15) have been reported for insomnia, depression, and anxiety in military and civilian samples. Thus, we conservatively estimated a NIM of *d* = 0.5 for each outcome of interest for this trial. The NIM of |*d*|= 0.5 set to determine non-inferiority is stringent as it represents 50% of the effect size reported in recent meta-analyses [61–63]. For non-inferiority tests, we set an allowable one-sided type I error rate of *α* = 0.025. Conservatively adjusting for our two a priori *t*-tests (post-treatment and a 3-month follow-up), we use *α** = 0.0125 to determine power. Based on the current patient volume and clinical workflows at the three participating sites, we estimated that a total of 188 patients could be enrolled in this clinical trial over the period of performance. Power calculations using PASS version 23.0.2. [64] yielded 88% power with a full sample of 94 participants per group (our primary strategy and 80% power with a final sample of 140 completers assuming an attrition rate of 25% (*N* = 70 completers per group).

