## Statistical methods

### Statistical methods for primary and secondary outcomes {20a}

Preliminary data analyses will be performed prior to testing the aims to check for collinearity of covariate and outcome measures, to ensure completeness and accuracy of data, and to evaluate distributions. The primary and secondary aims will be tested with non-inferiority hypotheses of the general form: H0: digital CBTI hubs are inferior to ICAU versus H1: digital CBTI hubs are non-inferior ICAU. For each outcome, we will calculate the standardized differences (Cohen’s *d*) as digital CBTI hubs—ICAU, such that a positive difference is in favor of ICAU if higher values are worse, and a negative difference is in favor of ICAU if higher values are better. Since higher values indicate worse outcomes for our measures of interest (e.g., ISI, depression, anxiety), we will use a non-inferiority margin (NIM) of 0.50 and declare digital CBTI hubs to be non-inferior to ICAU if the upper bound of the 95% confidence interval (CI) for *d* is ≥ 0.50. We will declare digital CBTI hubs to be inferior to ICAU if the upper bound of the 95% CI for *d* is ≤  − 0.50. For example, if *d* (95% CI) = 0.10 (− 0.20, 0.40), we would declare digital CBTI hubs as non-inferior to ICAU because 0.40 < 0.50. But if *d* (95% CI) = 0.40 (0.10, 0.70), we would declare digital CBTI hubs to be inferior because − 0.70 ≥ 0.50. These one-sided decision rules equate to requiring the effect size comparing digital CBTI hubs to ICAU to have no more than moderate strength (|*d*|= 0. 5) in favor of ICAU.

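### Power is computed at one-sided 0.0125 for each of two ISI time points, but each is judged with a 95% CI (one-sided 0.025), and no rule says whether one or both must succeed

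*Protocol article*

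**What the plan says.** On the error rate, the section on statistical methods {20a} states: "For non-inferiority tests, we set an allowable one-sided type I error rate of *α* = 0.025". Sample size {14} says the same. Both sections then halve this level because there are two planned comparisons, and {20a} limits the use of the halved level to power: "Conservatively adjusting for our two a priori *t*-tests (6–8 weeks and 3-month follow-up), we use *α = 0.0125 to determine power". On that basis both sections quote power of 0.88 with 94 per group and 0.80 with 70 completers per group.

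On the decision, {20a} defines non-inferiority through "the upper bound of the 95% confidence interval (CI) for *d" set against a margin of 0.50, and its worked examples use 95% intervals. For the primary outcome it plans an ANCOVA "to determine whether ISI at 6–8 weeks and at 3-month follow-up differs between digital CBTI hubs and ICAU", with effect sizes "with 95% CIs estimated from the ANCOVA model will be calculated and compared to the NIM as outlined above".

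Objectives {7} words the first hypothesis as non-inferiority after 6–8 weeks and at 3-month follow-up. Nothing in the protocol says whether success at one time point is enough, whether both are needed, or whether they are tested in a fixed order.

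**The concern.** An upper 95% confidence limit compared with a margin is a one-sided test at 0.025. The plan divides 0.025 between two tests when it computes power, then gives each test the full 0.025 when it decides. Splitting alpha protects against a false claim only if the split is applied to the decision, and here it is not.

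This is the decision rule for the primary outcome, and Methods for additional analyses {20b} makes the superiority tests depend on it. If a claim may rest on either time point, the false-claim rate is above the level the plan allows. If both are needed, the error rate is safe but the quoted power belongs to another rule. A statistical analysis plan cannot settle this quietly, because the protocol has already fixed the interval, the level, the number of tests and the power. If the interval is chosen after outcomes have been compared, the choice could look driven by the results.

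**Working it through.** **Inputs.** From Sample size {14} and {20a}: margin d = 0.5, one-sided alpha 0.025, per-test alpha for power 0.0125, 94 per group in full and 70 per group after 25% attrition. My assumptions: a true difference of 0, which the protocol does not state, and a correlation between the two test statistics of 0 to 0.9, for which it gives no figure. The printed inequality for non-inferiority in {20a} conflicts with that section's own worked example (0.40 < 0.50); I read the rule as upper limit below 0.50.

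**1. Reproduce the stated power.** In SD units, power per test = Φ(0.5·√(n/2) − z).
- n = 94: 0.5·√47 = 3.428. At 0.0125 (z = 2.241), Φ(1.186) = 0.882 (0.878 with the noncentral t). At 0.025 (z = 1.960), Φ(1.468) = 0.929.
- n = 70: 0.5·√35 = 2.958. At 0.0125, Φ(0.717) = 0.763 (0.755 with t). At 0.025, Φ(0.998) = 0.841 (0.836 with t).

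The stated 0.88 is reproduced at 0.0125 and not under the 95% interval rule. The stated 0.80 with 70 per group is reproduced at neither level.

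**2. Overall error if either time point supports a claim.** With the true effect at the margin at both visits, error = 1 − P(Z₁ < z, Z₂ < z), where (Z₁, Z₂) is bivariate normal with correlation ρ.

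| ρ | two 95% CIs | two 97.5% CIs |
|---|---|---|
| 0 | 4.9% | 2.5% |
| 0.3 | 4.8% | 2.4% |
| 0.5 | 4.5% | 2.3% |
| 0.7 | 4.2% | 2.2% |
| 0.9 | 3.5% | 1.8% |

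At ρ = 0 the first figure is 1 − 0.975² = 0.0494 and the second is 1 − 0.9875² = 0.0248.

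**3. Error and power if both must succeed.** A false joint claim requires passing at a time point where the true effect is at or beyond the margin, so the error is at most 0.025 with 95% intervals. Joint power = P(both pass):
- 94 per group: 0.929² = 0.863 at ρ = 0, rising to 0.905 at ρ = 0.9.
- 70 per group: 0.841² = 0.707 at ρ = 0, rising to 0.798 at ρ = 0.9.

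**4. Can the choice of interval change a verdict?** The largest observed d that passes is 0.5 − z·√(2/n).
- 94 per group (√(2/94) = 0.146): 0.214 with a 95% interval, 0.173 with a 97.5% interval.
- 70 per group (√(2/70) = 0.169): 0.169 with a 95% interval, 0.121 with a 97.5% interval.

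An observed d between these limits passes under one interval and fails under the other.

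**The case against.** The strongest reply is that the inflated error needs an either-time-point rule that the protocol never states. Objectives {7} joins the two visits with a conjunction, and if both must succeed, two 95% intervals hold 2.5% without adjustment. The 0.025 is also not called an overall or familywise rate. Read per test, it agrees with the 95% interval, and the halving could be a planner's safety buffer for sample size. Finally, for a single test the mismatch errs on the safe side for power: 0.93 against 0.88 with 94 per group, and 0.84 against 0.76 with 70.

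Most of this stands. A reader might infer that the trial will run at a 4.9% error rate, nearly twice what it allows. The documents do not support that. The 4.9% requires an unstated rule and uncorrelated tests, yet both tests use the same patients, so positive correlation is likely.

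The reply does not remove the mismatch. Under the conjunctive reading the split has no purpose and the quoted power is not that of the joint rule. Under the per-test reading, the protocol still adjusts for two tests in one place and not in the other. No reading makes the level, the interval and the power agree.

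**Conclusion.** The point holds as an internal inconsistency in the primary decision rule: alpha is split for power and not for the decision. Its consequence is conditional. If either time point suffices, the overall one-sided error is about 3.5–4.9% against 2.5%, for assumed correlations of 0.9 down to 0 and a true effect at the margin at both visits. If both are required, the error is controlled and the fault lies in the power statement: 86–90% with 94 per arm and 71–80% with 70, assuming a true difference of 0. The protocol fixes neither rule, so no single inflated error rate can be attributed to it. That the powered test differs from the planned test does not depend on the correlation or on which rule was meant.

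**What to change.** In {20a}, state whether a claim needs one or both time points, then match interval and power to that rule there and in Sample size {14}. Any of three versions is coherent:

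- **(a) Either time point.** Use two-sided 97.5% intervals, so that each upper limit is a one-sided 0.0125 test. Power per time point stays 0.88 with 94 per arm, but with 70 per arm it is about 0.76, and the stated 0.80 must be corrected. About 77 per arm would be needed for 0.80.
- **(b) Both time points.** Keep 95% intervals, drop the split, and quote joint power: 86–90% with 94 per arm and 71–80% with 70, with the correlation assumption stated. This stays closest to the wording of Objectives {7}.
- **(c) One primary time point.** Keep the 95% interval at the full one-sided 0.025 and quote about 0.93 with 94 per arm and 0.84 with 70. The other time point becomes secondary and its confirmatory claim is given up.

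The change is to wording only, with no new data or procedures. The price is wider intervals and lower power after attrition in (a), possibly lower joint power after attrition in (b), and one confirmatory claim in (c). The choice should be made before outcomes are compared by arm.
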